## Supplement 1: Study Protocol TORN-Project

| Project Information                                                 |
|---------------------------------------------------------------------|
| Title: Triggers Online Resulting in Non-suicidal Self-Injury |
| Acronym: TORN                                                |
| DRKS-ID: DRKS00025905                                        |
| Study Type: Experimental Study, Clinical                     |
| Registration type: Prospective                               |

### Brief summary in lay language

Non-suicidal self-injury (NSSI) is a major mental health concern for adolescents. To date, only factors that can trigger NSSI via digital media (e.g., via social media) have been poorly studied. Therefore, 50 (25 with NSSI and 25 healthy) adolescents aged 14 to 18 years will participate in a diary study and provide information about their emotional state, their internet usage and specific events over the duration of one week. This is to identify events in their daily lives that may lead to NSSI. In a further step, the same adolescents will participate in a second study. In this study, triggers for NSSI (e.g. certain words, details in pictures) will be analyzed by measuring eye movements. A final study will include 50 participants with NSSI (including the existing 25 participants with NSSI), in which the influence of social rejection on the perception of triggers from social media channels and the associated stress will be investigated.

### Brief summary in scientific language

**RATIONALE:** Non-suicidal self-injury (NSSI) represents a major worldwide mental health concern in adolescents. One of the underlying mechanisms of NSSI are the negative biases in processing social feedback from others. Especially the friendship groups in which peers engage in NSSI and experiences of social rejection are discussed as significant predictors for NSSI behavior. Both are prominent phenomena in digital social media, but only little is known about the triggering factors for NSSI behavior in online interactions (e.g. pictures, words, social dynamics).

**AIM:** We aim to address this paucity of research by conducting two laboratory studies and an ecological momentary assessment (EMA) over one week with an adolescent cohort. The three main objectives of this research project are (1) to investigate the purposes, risks, and benefits of social media related to NSSI in an everyday context using a 7-days real-life assessment, (2) to understand whether the presentation of wounds, scars, materials used for NSSI or words related to NSSI provoke arousal, behavioral activation or an urge or thoughts to NSSI, and (3) to explore if social exclusion alters the reactivity towards NSSI-related stimuli.

**METHOD:** The study uses EMA by means of a programmed smartphone app that allows patients to report events, affects, and experiences on a daily basis with an emphasis on social media usage and stress-related events. We will include 50 participants (n=25 patients with NSSI; n=25 healthy adolescents) in this phase of the project. Subsequently, these 50 participants will be invited to our first laboratory study using eye-tracking and psychophysiological measures during the presentation of NSSI-related stimuli to examine attentional bias, stimuli avoidance, autonomic reactivity and self-

report of perceived stress and NSSI-related cognitions. A third study will investigate the effect of social exclusion in 50 participants with a current history of NSSI on hormonal, physiological and reported subjective stress during exposure with NSSI-related material embedded in social media content.

**RESULTS/INNOVATION:** To our knowledge, this is the first study to investigate triggering effects of social media content in adolescents with NSSI conducting an everyday study as well as laboratory experiments. We study mechanisms that lead to NSSI using a multi-method approach including biological, behavioral and self-report measures to understand an issue that is highly relevant in clinical work.

| Health condition or problem studied             |
|-------------------------------------------------|
| Diagnosis:                               |
| Non-Suicidal Self-Injury                        |
| F60.3 Emotionally unstable personality disorder |
| Healthy volunteers:                      |
| Yes                                             |

  

| Interventions, Observational Groups                                                                                                                                                                                                                                                                                                                                                 |
|-------------------------------------------------------------------------------------------------------------------------------------------------------------------------------------------------------------------------------------------------------------------------------------------------------------------------------------------------------------------------------------|
| Arm 1:                                                                                                                                                                                                                                                                                                                                                                       |
| 
 
• Study 1: Ecological Momentary Assessment for one week with NSSI-patients.
 
• Study 2: Presenting neutral and NSSI-related stimuli for eyetracking in NSSI-patients.
 
• Study 3: Social exclusion (according to Cyberball) prior to a presentation of neutral and NSSI-related stimuli with NSSI-patients.
 
       |
| Arm 2:                                                                                                                                                                                                                                                                                                                                                                       |
| 
 
• Study 1: Ecological Momentary Assessment for one week with healthy controls.
 
• Study 2: Presenting neutral and NSSI-related stimuli for eyetracking in healthy controls.
 
• Study 3: Social inclusion (according to Cyberball) prior to a presentation of neutral and NSSI-related stimuli with NSSI-patients.
 
 |

  

| Endpoints                                                                                                                                                                                                                                                                                                                                                                                                                                                                  |
|----------------------------------------------------------------------------------------------------------------------------------------------------------------------------------------------------------------------------------------------------------------------------------------------------------------------------------------------------------------------------------------------------------------------------------------------------------------------------|
| Primary Outcome:                                                                                                                                                                                                                                                                                                                                                                                                                                                    |
| 
 
• Study 1: Urge/ideation to NSSI, NSSI frequency/intensity during 7 day period (EMA)
 
• Study 2: Urge/ideation to NSSI (self-rated), initial fixation & fixation time (both eye-tracking), autonomous response (SCR, HR) during experimental procedure
 
• Study 3: Cortisol stress response, heart rate response, initial fixation & fixation time (eye-tracking) during experimental procedure.
 
 |
| Secondary Outcome:                                                                                                                                                                                                                                                                                                                                                                                                                                                  |
| 
 
• Study 1: Mood, motives for NSSI (both, self-rated; ecological momentary assessment; duration: 7 days)
 
• Study 2: stress arousal/appraisal, positive and negative affect (all, self-rated), pupil dilatation (eyetracking) during experimental procedure
 
• Study 3: fundamental basic needs, stress arousal/appraisal, urge/ideation to NSSI (all, self-rated) during experimental procedure.
 
         |

  

| Study Design    |
|-----------------|
| Purpose: |
| Other           |

|                                      |
|--------------------------------------|
| Study Type:                   |
| Non-Interventional            |
| Longitudinal/cross-sectional: |
| Cross-sectional                      |

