### Statistical Plan:

We will use Multilevel Modeling (MLM) for analyzing data of the EMA study (assessing differences in event- and signal-based affective responses). The data of MLM will be fitted using lme4 package (Bates et al., 2015) and lmerTest package (Kuznetsova et al., 2017). Within-person (time) change will be depicted in level 1 and a between-person submodel in level 2, dunking how affective responses will vary between groups (NSSI vs. HC). For the Experimental Study 1 task involving NSSI-stimuli, we will perform a 2 (group NSSI vs non-NSSI patients) x 2 (stimuli quality: NSSI-related vs neutral) repeated measures ANOVA on our dependent variables (accuracy and reaction times) as well as post-experimental comparisons (e.g. NSSI urge, perceived stress). Statistical analyses for Experimental Study 2 include number of initial fixations, time of fixations, salivary cortisol, HR as well as SCR and psychological questionnaire data. Differences between socially excluded and included participants are analyzed using repeated measures Analysis of Variance (rmANOVA). A priori power analysis using G\*Power (Faul, Erdfelder, Lang, & Buchner, 2007) revealed that our study with a repeated measures design (main hypotheses) including n=50 participants per study will be efficiently powered to detect a medium effect size (i.e., interaction, Cohens  $f = 0.25$ , correlation among measurements  $r = 0.50$ ) with a power of  $1-\beta = 0.80$ . Our power calculations follow the suggestions by Cummings (2014). We expect to detect large effects (=clinically relevant) in between-subject analyses. The sample size of

$n=50$  for each study is within the recommended range of level 2 grouping variables to establish accurate estimates in multilevel-modeling (Maas & Hox, 2005) for analyzing EMA.

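### Study 3: where cortisol or heart rate response is measured against a pre-Cyberball value, adjusting for that value is more efficient than entering it as a level of the planned rmANOVA

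*Protocol*

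**What the plan says.** The protocol's Study 3 is the Experimental Study 2 of its Statistical Plan.

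- **Endpoints, Primary Outcome:** "Study 3: Cortisol stress response, heart rate response", together with two eye-tracking measures.
- **Statistical Plan, outcomes:** "Statistical analyses for Experimental Study 2 include number of initial fixations, time of fixations, salivary cortisol, HR as well as SCR", plus questionnaires.
- **Statistical Plan, method:** "Differences between socially excluded and included participants are analyzed using repeated measures Analysis of Variance (rmANOVA"). No baseline covariate is named.
- **Statistical Plan, power:** a repeated-measures interaction with f = 0.25, correlation r = 0.50 and power 0.80, "including n=50 participants per study".
- **Interventions, Arm 1:** "Social exclusion (according to Cyberball) prior to a presentation of neutral and NSSI-related stimuli with NSSI-patients". Arm 2 has inclusion in place of exclusion.
- **Aim, third objective:** "to explore if social exclusion alters the reactivity towards NSSI-related stimuli".

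The protocol does not give the cortisol or heart rate sampling times, the within-subject factor of the Study 3 rmANOVA, the split between conditions, or the way participants are allocated to them.

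**The concern.** A cortisol stress response is most naturally a change from a value taken before the social task. A repeated measures ANOVA uses that value as one more outcome occasion, as if the conditions could differ there. If allocation is independent of baseline they differ there only by chance, and the pre-task value does more good as a covariate.

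The change score subtracts the whole baseline difference. A regression on baseline subtracts only the fraction that carries over to the post value. With 25 per condition (an assumption), the standard error of a chance baseline difference is sqrt(2/25) = 0.28 SD. At r = 0.50, an imbalance of that size moves the change-score estimate by (1 - 0.50) x 0.28 = 0.14 SD in the opposite direction. This averages out over repetitions, so it is a loss of precision and not a bias. Still, Study 3 is small and the precision could be had without recruiting anyone.

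**Working it through.** **Inputs.** From the Statistical Plan: f = 0.25 for an interaction, r = 0.50, N = 50, power 0.80. Assumed because not stated: two-sided alpha 0.05, 25 per condition, two occasions, equal variances, allocation independent of baseline.

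**1. The plan's own figure.** For two groups and m = 2 measurements, the noncentrality is f² x N x m / (1 - r) = 0.0625 x 50 x 2 / 0.50 = 12.5, on 1 and 48 degrees of freedom. Power is 0.934, not 0.80. Power of 0.80 is reached at N = 34, or at N = 50 with f = 0.20. The stated 0.80 is matched only with inputs that the plan does not give, such as alpha 0.01 (0.799). The discrepancy is on the safe side and is not the point here.

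**2. Link to the change score.** In a 2 x 2 layout f = 0.25 is a difference in changes of 4 x 0.25 = 1.0 SD of a single measurement. The SD of a change is sqrt(2(1 - 0.50)) = 1.0, so the standardised difference is 1.0. The squared noncentrality of the t test is 1.0² x 25/2 = 12.5, the same as in step 1. The condition x time F is the square of the change-score t.

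**3. Variance with and without adjustment.** In units of the single-measurement variance, the change score has 2(1 - r), the baseline-adjusted post value has 1 - r², and the ratio is (1 + r)/2.

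| r | Change score | Adjusted | Ratio |
|---|---|---|---|
| 0.3 | 1.40 | 0.91 | 0.65 |
| 0.5 | 1.00 | 0.75 | 0.75 |
| 0.7 | 0.60 | 0.51 | 0.85 |
| 0.8 | 0.40 | 0.36 | 0.90 |

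These ratios treat the covariate slope as known. With the slope estimated at 25 per condition and r = 0.50, simulation gave ratios of 0.78 (10,000 runs) and 0.76 (4,000 runs), a reduction of 22% to 24%.

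**4. Power.** On the plan's inputs the noncentrality rises from 12.5 to 12.5/0.75 = 16.7, and power from 0.934 to 0.979. An effect of 0.81 SD of change has 80% power under the change score. Adjusted, it becomes 0.81/sqrt(0.75) = 0.93, with power 0.90. The simulation gave 0.80 and 0.90.

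**5. Other designs that the text allows.**

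- *Several post-task samples.* If their mean is compared with one baseline and all correlations are 0.50, the ratio is 0.50/0.75 = 0.67 for two samples and 0.375/0.625 = 0.60 for four. The omnibus condition x time test over three or more occasions is a different test and does not reduce to a change score.
- *Condition x stimulus.* If the contrast is NSSI-related minus neutral, both after Cyberball, its covariance with baseline is r - r = 0 under equal correlations. The gain from adjustment is then nil.

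**The case against.** The strongest reply is that the protocol does not describe the design in which these figures apply. It mentions no pre-Cyberball sample, and the third objective can be read as a condition x stimulus question, for which adjustment gains nothing. That reading is quite plausible for heart rate and natural for the fixation measures. It fits a cortisol stress response less well, because that endpoint calls for a reference value before the stressor. So the point stands for cortisol on the natural reading, and for heart rate only if it is scored against a resting pre-task value.

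Second, the advantage of a covariate presumes allocation independent of baseline. The protocol does not say how participants come to be excluded or included, and it combines existing with newly recruited patients. Without that independence, ANCOVA and change scores can answer different questions. This condition must be met before the fix is adopted.

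Third, baseline definitions and covariates are often left to an SAP, which may exist here. That is fair, and a missing detail would be no finding. But the protocol does name the method, and the suggestion concerns that choice.

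Fourth, computed power at the plan's effect size is already 0.93, and r = 0.50 is a generic planning value, not a measured cortisol or heart rate correlation. Both are true. They limit the size of the gain without removing it.

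**Conclusion.** The point holds conditionally, as an efficiency improvement. For a pre/post response with one value on each side and allocation independent of baseline, adjustment removes about a quarter of the change-score variance at r = 0.50, and 35% to 10% as r goes from 0.3 to 0.8. Power goes from 0.93 to 0.98 on the plan's inputs, or from 0.80 to about 0.90 for a smaller effect. These figures rest on 25 per condition and alpha 0.05, neither of which the protocol states for Study 3.

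A reader might infer more, and the document does not support it:

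- *That rmANOVA is wrong or biased here.* It is a valid analysis, and the loss is in precision only.
- *That the Study 3 rmANOVA is by its nature a change-score test.* That is so only with one pre and one post value, and the protocol fixes neither the occasions nor the within-subject factor.
- *That every Study 3 primary outcome would gain.* Condition x stimulus contrasts would gain about nothing.
- *That Study 3 is underpowered for its stated effect.* The recomputed power is above the stated 0.80.

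**What to change.** In the Statistical Plan, state for Study 3 whether each response is measured against a pre-Cyberball value and how participants are allocated to exclusion or inclusion. Given allocation independent of baseline:

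- **Cortisol, and heart rate if scored against a resting pre-task value:** analyse the post-task values with condition as the factor and the pre-Cyberball value as a covariate. Use ANCOVA for one post-task value. For several, use a mixed model of the post-task samples with baseline and baseline x time.
- **Fixation measures and other condition x stimulus contrasts:** keep the rmANOVA.

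The cost is a change of wording and one degree of freedom for the ANCOVA covariate. Any response scored against a pre-task value already needs that measurement, so no extra participants or samples are required.

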#### Recruitment Locations

- Recruitment countries: Austria
- Number of study centers: Monocenter study
- Recruitment location(s): University Medical Center : Universitätsklinikum für Kinder- & Jugendpsychiatrie, Wien Wien
- Planned study start date: 2022-05-01
- Actual study start date: 2022-06-01
- Target Sample Size: 50 per study
- Final Sample Size: No Entry

| Inclusion Criteria                                                                                                                                                                                                                                                                                                                                      |
|---------------------------------------------------------------------------------------------------------------------------------------------------------------------------------------------------------------------------------------------------------------------------------------------------------------------------------------------------------|
| Sex: All                                                                                                                                                                                                                                                                                                                                         |
| Minimum Age: 14 Years                                                                                                                                                                                                                                                                                                                            |
| Maximum Age: 18 Years                                                                                                                                                                                                                                                                                                                            |
| Additional Inclusion Criteria:
Inclusion criteria for the clinical group are (a) good German language skills, (b) fulfilling NSSI within the past 12 month after SITBI-G, (c) aged between 14;00 and 17;11 years. Inclusion criteria for the healthy controls are (a) good German language skills and (b) aged between 14;00 and 17;11 years. |

| Exclusion Criteria                                                                                                                                                                                                                                                                                                                                                                                                                                                                                                                                                                                                                                                                                                          |
|-----------------------------------------------------------------------------------------------------------------------------------------------------------------------------------------------------------------------------------------------------------------------------------------------------------------------------------------------------------------------------------------------------------------------------------------------------------------------------------------------------------------------------------------------------------------------------------------------------------------------------------------------------------------------------------------------------------------------------|
| Exclusion criteria for the clinical group are (a) adolescents treated with cortisone or suffering from a hormonal dysfunction, (b) fulfilling criteria for an Autism Spectrum Disorder (ASD), (c) IQ < 70 based on previous IQ-tests or clinical impression, (d) any known medical illness or other severe comorbid mental disorder requiring immediate treatment, (e) acute suicidality or severe aggression. Exclusion criteria for the healthy controls are (a) evidence of any current mental disorder or physical disease, (b) adolescents treated with cortisone or suffering from a hormonal dysfunction, (c) IQ < 70 based on previous IQ-tests or clinical impression, (d) acute suicidality or severe aggression. |

| Addresses                                                                                                                                              |                                                                                                                                                                                                        |
